### Analysis

We will tabulate the characteristics of included trials and the risk of bias assessments of the three groups of raters (minimal training, intensive training, and experienced raters); before and after consensus. We will then calculate the chance-corrected weighted Kappa with 95% confidence intervals to quantify agreement within and between the three groups of raters for each of the domains of the risk of bias tool. To calculate between-group Kappa agreement, we will use risk of bias assessments from pairs of raters after resolution of disagreements. Kappa values range from 0 to 1, with higher values indicating higher agreement between raters. To calculate the weighted Kappa agreement, risk of bias classification will be ordered as follows: low, unclear, and high risk of bias. Criteria proposed by Byrt
[13] will be used to interpret Kappa values. Values between 0.93 and 1.00 represented excellent agreement; 0.81 and 0.92 very good agreement; 0.61 and 0.80 good agreement; 0.41 and 0.60 fair agreement; 0.21 and 0.40 slight agreement, 0.01 and 0.20 poor agreement; and 0.00 or less will be considered to reflect no agreement.

The main outcome of our study is the comparison of the accuracy of assessment across groups, that is, a comparison of the agreement between raters receiving intensive training and experienced raters with the agreement between raters receiving minimal training and experienced raters. To compare agreement of raters under different training conditions, we will calculate the differences between Kappa values for within- and between-group agreement. To address deviations from normal distribution, we will bootstrap the difference in Kappa values using bias correction and acceleration to derive 95% confidence intervals and *P*-values
[14]. Please see Additional file
2 for assumptions used for the power analysis.

To explore whether quality of reporting influences agreement, we will stratify the analysis according to publication date (before the first CONSORT statement revision in 2001 vs 2001
[15] and later; and before the latest CONSORT statement revision in 2010
[16] vs 2010 and later), assuming that reporting quality of RCTs in physical therapy improved after the publication of the CONSORT statement

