[17, 18]. To investigate whether methodological quality influences agreement between raters, we will stratify the analysis by trial size (<100 and ≥100 patients randomized per trial arm), assuming that trial size is associated with methodological quality
[19]. A sensitivity analysis will be conducted on larger (≥100 patients randomized per trial arm) trials published after 2010 (i.e. after the latest revision of the CONSORT statement was published). All *P*-values will be two-sided. Analysis will be conducted in STATA, release 13 (StataCorp, College Station, TX).

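### The stratified analyses are meant to show whether reporting or methodological quality influences agreement, but no interval is planned for the between-stratum difference in Kappa

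*Protocol article*

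**What the plan says.** All the relevant text is in the Analysis section of the protocol article.

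- **Estimates.** The authors will calculate "chance-corrected weighted Kappa with 95% confidence intervals to quantify agreement within and between the three groups of raters", separately for each risk of bias domain.
- **Differences.** "To compare agreement of raters under different training conditions, we will calculate the differences between Kappa values for within- and between-group agreement". For inference, "we will bootstrap the difference in Kappa values using bias correction and acceleration to derive 95% confidence intervals", together with P-values. The section defines no other difference in Kappa.
- **Reporting quality.** "To explore whether quality of reporting influences agreement, we will stratify the analysis according to publication date". There are two splits, at 2001 and at 2010, each tied to a revision of the CONSORT statement.
- **Methodological quality.** "To investigate whether methodological quality influences agreement between raters, we will stratify the analysis by trial size". The cut is "<100 and ≥100 patients randomized per trial arm".
- **P-values.** "All *P*-values will be two-sided". The article does not say whether P-values will be produced inside strata.

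The section names neither a difference in Kappa between strata nor a training-by-stratum contrast.

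**The concern.** Asking whether reporting or methodological quality influences agreement means asking whether Kappa differs between early and late trials, or between small and large trials. The method named for this is stratification, and the only contrast in the stratified analysis compares intensive with minimal training. Repeated within a stratum, that contrast addresses whether the two training schemes agree equally well with the experienced raters in those trials. It does not compare one stratum with the other.

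Without an interval for the between-stratum difference, a reader has only separate stratum results to set side by side. Informal reading of such results can suggest an influence where strata differ by chance or by size, and it can miss one that is there. What is at stake is the soundness of any secondary statement about trial quality and agreement. The main comparison of training groups is not at stake.

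**Working it through.** **1. Match each question to the planned output**

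| Item | Contrast | Interval planned? |
|---|---|---|
| Main outcome | Kappa(intensive v experienced) − Kappa(minimal v experienced) | Yes, BCa bootstrap |
| Stratified, training | The same difference inside one stratum | Presumably, if the whole analysis is stratified |
| Stratified, agreement | Kappa in stratum A; Kappa in stratum B | Yes, one for each Kappa |
| The question asked | Kappa in stratum A − Kappa in stratum B | None named |

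**2. What interval overlap amounts to**

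The article gives no figure to reproduce here. Take two independent strata whose Kappas each have standard error s.

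- The 95% intervals fail to overlap when |K_A − K_B| > 2 × 1.96 × s.
- The standard error of the difference is s√2, so non-overlap requires |z| > 2 × 1.96/√2 = 2.77.
- The two-sided tail area beyond 2.77 is 0.0056, an alpha of about 0.6% rather than 5%.
- If a direct test has 80% power, the true difference is 1.96 + 0.84 = 2.80 standard errors. Power by non-overlap is Φ(2.80 − 2.77) = 0.51.
- If the direct test has 90% power, the difference is 1.96 + 1.28 = 3.24 standard errors. Power by non-overlap is Φ(3.24 − 2.77) = 0.68.

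The overlap reading is therefore conservative. Its cost is missed differences rather than false ones.

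**3. Illustration by simulation**

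The number of trials is not in the article, and the power assumptions are in an additional file that is not shown. Every input below is assumed: category shares 0.40/0.35/0.25, linear-weighted Kappa with the experienced raters of 0.4 or 0.7, and three stratum splits. Inference used a percentile bootstrap over trials (not BCa), with 400 resamples and 600 simulated studies per setting.

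*Scenario A: agreement differs between strata (0.4 v 0.7), with no training effect.*

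| Trials per stratum | Training difference significant, stratum A / B | Between-stratum difference detected |
|---|---|---|
| 50 / 50 | 9.5% / 8.3% | 82% |
| 30 / 70 | 8.8% / 5.3% | 75% |
| 20 / 100 | 9.0% / 6.5% | 67% |

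The within-stratum training test rejects in about 5% to 10% of studies, so it carries almost no information about the question asked. The between-stratum contrast, here averaged over the two training groups, does address it.

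*Scenario B: training effect (0.7 v 0.4), with identical strata.*

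| Trials per stratum | Significant in exactly one stratum | Between-stratum difference rejects | Difference of training differences rejects |
|---|---|---|---|
| 50 / 50 | 48% | 6% | 6% |
| 30 / 70 | 53% | 6% | 6% |
| 20 / 100 | 64% | 7% | 9% |

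When the strata are in fact identical, they often disagree on significance, while the direct contrasts stay near or somewhat above 5%. Scenario B concerns the training effect, which is not quite the article's question about agreement.

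**The case against.** The best case for the plan has four parts.

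*The question is not left unanswered.* The analysis includes Kappas with 95% intervals for all rater groups and pairings, and stratifying it would show agreement in early and late trials, and in small and large ones. This stands. A reader might infer that the training comparison is the only planned output and that the question gets no answer at all, but the text does not support that. What is missing is an interval for the difference.

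*The harmful readings are not in the plan.* A reader might infer that influence will be declared when the training effect is significant in one stratum only, or when intervals do not overlap. The article states neither rule, and P-values within strata are themselves an inference from the word stratify. This also stands. The simulated discordance rates are therefore not error rates of this plan. They show why those readings should not fill the gap.

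*These are secondary analyses in a pilot study, reported in a condensed article.* The publication-date analysis is worded as exploratory, and a fuller plan may name the contrast. This lowers the severity. It does not remove the point, because the article names a method for the question and that method gives no interval for the contrast asked about. Exploratory status relaxes error control, but the estimate should still match the question.

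*The remedy adds contrasts and the intervals will be wide.* This is true and is a real cost. A wide interval would nevertheless show openly how little the data can settle, which two separate Kappas do not.

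**Conclusion.** The point holds as a minor mismatch between question and contrast in the secondary analyses. As written, the stratified analyses describe agreement within strata but provide no interval for the difference between strata.

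The one size that does not depend on assumed trial numbers or Kappas is that of the overlap reading: an alpha of about 0.6%, and power of 51% where a direct test has 80%. It assumes independent strata, approximate normality and equal standard errors. The simulated rates are illustrations under assumed trial numbers, Kappas and category shares, and should not be quoted as properties of this study. The main outcome is not affected.

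**What to change.** Keep the three splits and add one or two sentences to the Analysis section:

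- For each split (2001, 2010, trial size) and each rater comparison, bootstrap the between-stratum difference in Kappa. Resample trials separately within each stratum, keep all ratings of a trial together, and report a 95% interval.
- If a differing training effect is also of interest, do the same for (intensive − minimal in stratum A) − (intensive − minimal in stratum B).
- Label these contrasts exploratory. Base any statement that quality influences agreement on them, and not on comparing stratum P-values or on interval overlap.

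**Cost.** The change takes a few lines of bootstrap code and needs no new data or raters. The intervals will be wide, and many may leave the question open. The contrasts are also several: three splits by at least four domains (counting blinding once) give 3 × 4 = 12 for each rater comparison. The exploratory label and reporting by intervals are therefore needed.

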## Discussion

This study will investigate whether the reliability of the risk of bias tool can be improved by training raters using standardized instructions for risk of bias assessment. We will calculate Kappa coefficients to quantify the agreement between experienced raters and inexperienced raters. Two inexperienced raters will receive intensive training on risk of bias assessment and the other two will receive minimal training. By including a control group with minimal training, we will attempt to mimic what many review authors commonly have to do, that is—conduct risk of bias assessments of RCTs without any formal training or standardized instructions. If our results indicate that an intensive standardized training does improve the reliability of the risk of bias tool, our study is likely to help improve the quality of risk of bias assessment, which is a central component of evidence synthesis
[4]. The standardized training package for risk of bias assessment could then be used by organizations such as the Cochrane Collaboration and the systematic review community at large. By publishing this protocol, we would also like to make the objectives and pre-specified study design transparent to readers, as has been recommended for methodological studies
[20].

### Strengths and limitations

Our study had two major strengths. First, we will include raters completely inexperienced with the risk of bias assessment to investigate the effect of intensive training on the reliability of the risk of bias tool. By including inexperienced raters, we believe we will be more likely to observe an effect of intensive training, if one indeed exists. If raters were already experienced with the risk of bias assessment, there could be limited room for improvement as postulated in a previous study that investigated the effect of training on a similar method for methodological quality assessment
[21]. Second, raters will be randomly allocated to training groups, and central randomization will be performed to conceal the random sequence of allocation. We acknowledge that this approach may not create a balanced distribution of potential confounders across the two training groups due to the low number of individuals randomized, but the group of students randomized will be fairly homogeneous and confounding therefore unlikely.

Our results can potentially be influenced by performance bias. If raters in the control group understand that they are not receiving the best training available in our study, they may feel discouraged to try and perform risk of bias assessments as best as they can. This could in turn lead to an artificially lower reliability of the risk of bias tool with minimal training as compared to intensive training. Alternatively, they could seek additional training elsewhere or be prompted to self-study. To try and minimize the risk of such performance bias, raters will not be informed to which training group they have been randomized, and they will be instructed to not discuss with each other any characteristics of their training. The use of minimal training as a control intervention may lead to an underestimation of the effect of our intensive training, however. Although ‘no training’ could be used as a control intervention instead of minimal training, this could substantially increase the risk of performance bias in our study, as explained above.

Although the standardized instructions were primarily based on the Cochrane Handbook instructions for risk of bias assessment, we added or adapted some of the criteria to facilitate raters’ decision-making in the present investigation. Some of these criteria are not solely based on empirical evidence but also on our own experience with analyses of individual RCTs and meta-analyses of RCTs (Additional file
1). The main example concerns the assessment of incomplete outcome data. To facilitate decision-making, we used thresholds of drop-out rates to define low and high risk of bias for assessing incomplete data. These thresholds were chosen based on evidence that this drop-out rate could be linked to biases
[22, 23]. Moreover, some of these adaptations may not apply to systematic reviews with different research questions. For instance, because outcomes in our sample of physical therapy trials could potentially be influenced by at least some degree of performance bias, blinding of patients and therapists were by definition deemed necessary. Conversely, the Cochrane Handbook recommends that raters first assess the need for patient and therapist blinding in each trial in light of the outcome of interest and to take this information into consideration when assessing the risk of performance bias. Although we fully agree with this recommendation, it was not included in our standardized instructions for the reason explained above.

The low number of raters randomized to intervention groups will be a limitation for the generalizability of our findings. Due to feasibility issues, we included the minimal number of participants needed to calculate Kappa agreements within each study condition. If results of the present investigation indicate that intensive training may indeed improve the reliability of the risk of bias tool, a future study including a larger number of raters could replicate our methods to address this limitation. Generalizability may be further hindered by the characteristics of the trials assessed in our study and of the individual providing the training on risk of bias assessment. Accuracy of the risk of bias assessment could vary if trials with different patient populations, interventions, and outcomes were assessed. Likewise, the quality of the training on the risk of bias assessment may vary according to the skills of the person who provides the training and the method used to deliver such training.

### Previous research

The risk of bias tool has been extensively used in many Cochrane reviews, albeit the information of the inter-rater reliability of the risk of bias tool is rather limited. To date, five studies
[9, 10, 24–26] have investigated the inter-rater reliability of the risk of bias tool, but none have proposed and investigated ways to improve its reliability. The inter-rater agreement for the individual domains of the risk of bias tool has been found to range from poor (Kappa = 0.13 for selective reporting) to substantial (Kappa = 0.74 for sequence generation)
[25]. Our team recently investigated the between-group Kappa agreement of the risk of bias tool comparing ratings from Cochrane reviewers to ratings from our team
[8]. Most of our Kappa values were considerably higher than those reported in previous studies. We suspect two key factors may explain these differences. Although we used the Cochrane Handbook guidelines for risk of bias assessments, we first predefined specific decision rules to assess the individual domains of the tool. Second, we used an intensive training for the raters to standardize the decision-making process. This could partly explain the results of our previous study. The current study will investigate this hypothesis.

## Abbreviations

*RoB*: risk of bias
*RCT*: randomized clinical trial
*PROSPERO*: international prospective register of systematic reviews
*CONSORT*: consolidated standards of reporting trials.
